## Abstract

**Introduction:**

Pancreatic cancer remains a leading cause of death with poor prognosis. Current standard chemotherapies offer limited survival benefits, and no standard treatment exists for patients failing two lines of therapy. Preclinical evidence suggests that targeting MNK and VEGFR pathways can remodel the immunosuppressive tumor microenvironment and enhance immunotherapy efficacy. This study evaluates the safety and efficacy of JDB153 (an MNK/VEGFR inhibitor) combined with serplulimab (an anti-PD-L1 antibody) in refractory advanced pancreatic cancer.

**Methods and analysis:**

This is a prospective, open-label, single-center, phase Ib/II clinical trial (NCT07175389). It will enroll patients with advanced pancreatic adenocarcinoma who have progressed after standard therapies. The study follows a Simon’s two-stage design. The initial phase will enroll 10 patients to test safety and preliminary efficacy. Patients will receive oral JDB153 and intravenous serplulimab. If at least one patient responds, the study will expand to a total of 32 patients. The primary endpoints are safety and ORR. Secondary endpoints include DFS, OS, and PFS. Safety will be graded using NCI-CTCAE version 5.0. Comprehensive biomarker analyses (PD-L1 expression, spatial immune profiling, next-generation sequencing, et al.) are integrated.

**Discussion:**

Patients with advanced pancreatic cancer need effective options that are less toxic than chemotherapy. Immunotherapy alone often fails in this disease due to the immunosuppressive microenvironment. By combining MNK/VEGFR inhibition with PD-1 blockade, this study investigates a promising strategy to overcome immune resistance and establish a novel treatment paradigm for advanced pancreatic adenocarcinoma.

## Introduction

1

Pancreatic cancer remains a formidable global health challenge, ranking as the sixth leading cause of cancer-related mortality worldwide (Bray et al., 2024). Characterized by an insidious onset and rapid progression, approximately 80% of patients are diagnosed at an advanced stage (Li et al., 2004; Ryan et al., 2014), resulting in a 5-year survival rate of merely 13% (Siegel et al., 2025).

Current first-line treatments for advanced pancreatic cancer predominantly rely on chemotherapy regimens, specifically FOLFIRINOX (irinotecan, 5-fluorouracil/leucovorin, and oxaliplatin), GnP (gemcitabine plus nab-paclitaxel), and NALIRIFOX (liposomal irinotecan, 5-fluorouracil/leucovorin and oxaliplatin) (National Comprehensive Cancer Network, 2025). The PRODIGE 4/ACCORD 11 trial demonstrated a median overall survival (OS) of 11.1 months with FOLFIRINOX, significantly outperforming gemcitabine monotherapy (Conroy et al., 2011). Similarly, the MPACT study showed that the GnP regimen improved OS to 8.5 months (Von Hoff et al., 2013). Despite these advances, the median progression-free survival (PFS) remained disappointing, at roughly 6 months, and over half of patients experienced disease progression or death within 1 year (Conroy et al., 2011; Von Hoff et al., 2013). Even the recent NAPOLI-3 study indicated that while NALIRIFOX improved OS compared to GnP (11.1 months vs. 9.2 months), the PFS was still limited to 7.4 months (Wainberg et al., 2023).

The situation for second-line treatment is also difficult and generally follows a cross-over chemotherapy principle (National Comprehensive Cancer Network, 2025). While studies have confirmed the efficacy of 5-fluorouracil-based regimens after gemcitabine failure and the benefit of gemcitabine-based regimens after 5-fluorouracil failure, the median OS in the second-line setting rarely exceeds 7 months (Wang-Gillam et al., 2016; Oettle et al., 2014; De La Fouchardière et al., 2024). Crucially, there is no established standard care for third-line treatment, necessitating the development of novel and effective subsequent therapies (National Comprehensive Cancer Network, 2025).

Pancreatic cancer is characterized by abnormal blood vessel formation and high interstitial pressure, creating a barrier that prevents immune cells from entering the tumor (Li et al., 2019). Targeting the vascular endothelial growth factor receptor (VEGFR) can normalize these blood vessels and remodel the immunosuppressive microenvironment, thereby facilitating cytotoxic T cells infiltration and enhancing antitumor immunity (Goel et al., 2011; Liu et al., 2022). However, no antiangiogenic agents or immunotherapy have been approved for pancreatic cancer to date. This unmet need underscores the urgency of identifying novel therapeutic targets and combination strategies to improve outcomes in this refractory disease.

The regulation of protein translation plays a vital role in gene expression, and eIF4E is a core component of this process (Sonenberg and Hinnebusch, 2009; Chen et al., 2023). EIF4E initiates protein synthesis by binding the mRNA 5′-cap to form the eIF4F complex (Sonenberg and Hinnebusch, 2009; Chen et al., 2023). Its activity is strictly regulated by the Ras/Raf/MEK/ERK/MNK and PI3K/Akt/mTOR pathways, particularly through phosphorylation at Ser209 b y MNK kinases (Fabbri et al., 2021; Jin et al., 2021; Fernandez et al., 2023). EIF4E is often overexpressed in pancreatic cancer, and drives the translation of oncogenic proteins that are related to tumor growth, metastasis, drug resistance, and poor prognosis (Ma et al., 2019; Adesso et al., 2013; Fang et al., 2025; Li et al., 2024). Preclinical research shows that eFT508, a MNK kinase inhibitor, significantly reduces the proliferation and survival of pancreatic cancer cell lines by inducing apoptosis (Li et al., 2024). Blocking MNK can inhibit tumor growth without affecting normal cells, making it a safe therapeutic target (Jin et al., 2021; Li et al., 2024).

Furthermore, MNK inhibition reconfigures the immune microenvironment and enhances immunotherapy through multiple mechanisms (Figure 1) (Bartish et al., 2023). Preclinical studies across various malignancies demonstrates that inhibiting MNK-mediated eIF4E phosphorylation selectively decreases PD-L1 protein expression on tumor cells, dendritic cells, and myeloid-derived suppressor cells (MDSCs) (Xu et al., 2019; Cerezo et al., 2018; Huang et al., 2021; Guo et al., 2021). Additionally, blocking the MNK1/2-eIF4E axis impairs the production of pro-inflammatory factors like CCL5, and reduces the recruitment of immunosuppressive myeloid cells while increasing the infiltration and cytotoxic activity of CD8^+^ T cells (Xu et al., 2019; Huang et al., 2021; Guo et al., 2021).

**FIGURE 1 F1:**
[figure not shown]
Mechanism of the dual MNK/VEGFR inhibitor JDB153 synergizing with anti-PD-1 therapy in pancreatic cancer. This diagram illustrates the synergistic therapeutic mechanism of JDB153 and serplulimab. Centrally, the MNK1/2-eIF4E axis integrates oncogenic signals from the MAPK and PI3K pathways to selectively drive the translation of pro-tumorigenic mRNAs, including PD-L1 and CCL5. By inhibiting MNK, JDB153 directly downregulates PD-L1 protein expression on tumor cells and immunosuppressive myeloid cells (MDSCs/DCs), thereby lowering the threshold for T cell activation. Simultaneously, its VEGFR inhibition facilitates vascular normalization, reducing interstitial fluid pressure and alleviating the physical barriers characteristic of the pancreatic cancer microenvironment. This dual action reshapes the cold tumor microenvironment into a hot one, characterized by significantly increased infiltration and cytotoxic function of CD8^+^ T cells. Combined with the anti-PD-1 antibody serplulimab, this strategy overcomes immunotherapy resistance, offering a potent approach to enhance anti-tumor immunity in advanced pancreatic adenocarcinoma. Abbreviations: CCL5, C-C motif chemokine ligand 5; DCs, dendritic cells; MDSCs, myeloid-derived suppressor cells; MNK, mitogen-activated protein kinase-interacting kinase; PD-1, programmed cell death protein 1; PD-L1, programmed death-ligand 1; VEGF, vascular endothelial growth factor; VEGFR, vascular endothelial growth factor receptor.

JDB153 is a novel dual inhibitor targeting both MNK and VEGFR. In lung cancer models, JDB153 has demonstrated potent antitumor efficacy by inhibiting cell proliferation and angiogenesis, and reshapes the tumor microenvironment by increasing the infiltration of CD8^+^ T cells (Xu et al., 2025). Immune checkpoint inhibitors (ICIs) have shown safety but limited efficacy in pancreatic cancer (Marabelle et al., 2020; Renouf et al., 2022; Fu et al., 2023; Cheng et al., 2024; Wainberg et al., 2020; Kamath et al., 2020). Although no clinical study has yet investigated the efficacy of JDB153 in combination with immunotherapy, we hypothesize that JDB153 can synergize with serplulimab, an anti-PD-1 antibody, to enhance the immune response against pancreatic adenocarcinoma, thereby improving the overall therapeutic efficacy. This synergistic effect is anticipated to overcome immunotherapy resistance mechanisms, offering a novel and potentially more effective treatment strategy for advanced pancreatic adenocarcinoma. This study aims to evaluate the safety and efficacy of JDB153 combined with serplulimab in patients with advanced pancreatic cancer who have failed standard therapies.

## Methods and analysis

2

This study is a prospective, open-label, single-center, phase Ib/II clinical trial, and will be conducted at the West China Hospital, Sichuan University. The trial has received approval from the Ethics Review Committee of West China Hospital, Sichuan University, and is registered with ClinicalTrials.gov (NCT07175389). The reporting of this protocol follows the Standard Protocol Items: Recommendations for Interventional Trials (SPIRIT) guidelines (Figure 2).

**FIGURE 2 F2:**
[figure not shown]
Study Design and Participant Flow Abbreviations: BID, twice daily; CR, complete response; DCR, disease control rate; DLT, dose-limiting toxicity; DoR, duration of response; ECOG, Eastern Cooperative Oncology Group; HSP90α, heat shock protein 90 alpha; IV, intravenous; MMR, mismatch repair; N, number of patients; NGS, next-generation sequencing; ORR, objective response rate; OS, overall survival; PD-L1, programmed death-ligand 1; PFS, progression-free survival; PO, orally; PR, partial response; Q3W, every 3 weeks; RECIST, Response Evaluation Criteria in Solid Tumors; TTP, time to progression.

### Study objectives

2.1

The primary objective of this study is to evaluate the safety and efficacy of JDB153 tablets combined with serplulimab injection in patients with advanced pancreatic cancer who have experienced disease progression following standard treatments.

The primary endpoints focus on safety profile and objective response. Safety is assessed based on adverse events (AEs) graded via the National Cancer Institute Common Terminology Criteria for Adverse Events (NCI-CTCAE) version 5.0, including the incidence of dose-limiting toxicities (DLTs), serious adverse events (SAEs), and treatment-related adverse events (TRAEs). Efficacy is primarily measured by the objective response rate (ORR), defined as the proportion of patients achieving complete response (CR) or partial response (PR) according to Response Evaluation Criteria in Solid Tumors (RECIST) version 1.1.

Secondary endpoints include the disease control rate (DCR), as well as OS, PFS, duration of response (DoR), and time to progression (TTP). DCR is defined as proportion of patients achieving CR, PR, and stable disease (SD). OS is defined as the time from study enrollment to death from any cause. PFS is defined as the time from study enrollment to the first documented disease progression or death. DoR is defined as the time from first documented objective response (CR or PR) to disease progression or death, and TTP is defined as the time from study enrollment to disease progression.

### Study design

2.2

The study employs a Simon’s two-stage design, which permits early termination for futility and minimizes patient exposure to an ineffective regimen. The initial phase (phase Ib) will enroll 10 participants to evaluate the safety and preliminary efficacy of the combination. Patients will receive JDB153 at a dose of 600 mg orally twice daily (BID) and serplulimab at a dose of 200 mg via intravenous infusion every 3 weeks. If no patient achieves an objective response, the study will be terminated. The study will also be terminated in the event of unresolved SAEs or death. If one or more patient achieves, the trial will proceed to phase II. This phase will enroll additional patients to reach a total sample size of 32. If more than one patient in the phase Ib experiences a DLT, the dose of JDB153 for the phase II cohort will be reduced to 500 mg orally BID. Otherwise, the dose will remain at 600 mg orally BID. If DLT occur in one or more patients at the 500 mg BID dose level, the study will be terminated. If four or more responses are observed among the 29 evaluable patients, the null hypothesis will be rejected, indicating that the regimen merits further investigation.

Treatment will continue until documented disease progression (PD), intolerable AEs, withdrawal of consent by the patient, or a maximum duration of 24 months.

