### Eligibility criteria

2.3

The study population consists of patients with histologically or cytologically confirmed locally advanced or metastatic pancreatic adenocarcinoma and must have experienced disease progression after at least one line of standard systemic therapy (Table 1). Additional key inclusion criteria require patients to be between 18 and 75 years of age, have a life expectancy of at least 12 weeks, and maintain an Eastern Cooperative Oncology Group (ECOG) performance status of 0 or 1. Patients must possess at least one measurable lesion according to RECIST version 1.1.

**TABLE 1 T1:** Inclusion and exclusion criteria for patient selection.

Item	Criteria description
Inclusion criteria	
Diagnosis	Histologically or cytologically confirmed locally advanced unresectable or metastatic pancreatic adenocarcinoma
Demographics	Age between 18 and 75 years, male or female
Life expectancy	Life expectancy of at least 12 weeks
Performance status	ECOG performance status of 0 or 1
Prior therapy	Disease progression following standard systemic therapy. Disease progression occurring during or within 6 months of completing adjuvant chemotherapy is considered as failure of one line of systemic therapy
Measurable disease	Presence of at least one measurable lesion according to RECIST v1.1. Longest diameter ≥10 mm if measured by spiral CT or ≥20 mm if measured by conventional CT or MRI.
Organ function	Adequate bone marrow and organ function, defined by laboratory results obtained within 7 days prior to enrollment. Patients must not have received blood transfusion, granulocyte colony-stimulating factor, or other medical supportive treatment within 14 days prior to the first dose of study drug • Hemoglobin: ≥90 g/L • Platelets: ≥75 × 10^9/L • White blood cells: ≥3.0 × 10^9/L • Absolute neutrophil count: ≥1.5 × 10^9/L • Total bilirubin: ≤1.5× ULN (≤3× ULN if liver metastases are present) • ALT and AST: ≤2.5× ULN (≤5× ULN if liver metastases are present) • Creatinine: ≤1.5× ULN.
Informed consent	Voluntary participation with a signed and dated written informed consent form
Exclusion criteria	
Prior malignancy	History of other malignant tumors with disease free survival <5 years. Exceptions include cured basal cell carcinoma of the skin, cured cervical carcinoma *in situ*, and gastrointestinal tumors cured via endoscopic mucosal resection
Prior immunotherapy	Prior treatment with anti-PD-1, or anti-PD-L1 inhibitors

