### Data collection and assessments

2.5

Tumor response will be evaluated every 8 weeks according to RECIST version 1.1. Given the mechanism of immunotherapy, pseudoprogression is a possibility. If disease progression is suspected radiologically but the patient is clinically stable, treatment may continue, and a confirmatory scan will be performed at least 4 weeks later, utilizing irRECIST criteria.

Safety will be assessed continuously throughout the study. Adverse events will be graded according to NCI-CTCAE version 5.0. Assessments will include physical examinations, ECOG performance status, and comprehensive laboratory panels (complete blood count, urinalysis, blood biochemistry, coagulation, tumor markers, cardiac enzymes, and thyroid function) performed within 1 week prior to the start of each new cycle. QoL scores will be collected every 8 weeks.

As the single-agent pharmacokinetic profile of JDB153 has been established in a prior phase I study (unpublished data), sparse sampling in cycle one combined with trough concentration monitoring in subsequent cycles is sufficient to assess potential drug-drug interactions while minimizing patient burden. Blood samples will be collected pre-dose, and at 2, 4, and 8 h post-dose in cycle 1 only.

Biomarker exploration is a key component of this trial. Patients will consent to the use of archival tumor tissue previously obtained and blood samples collected within 1 week prior to treatment. Analyses will include PD-L1 expression, mismatch repair (MMR) status, single-cell spatial proteomics and transcriptomics, and next-generation sequencing (NGS). PD-L1 is evaluated as a predictive marker for immunotherapy response and is mechanistically linked to JDB153 activity via MNK-eIF4E-mediated translational regulation. Peripheral blood markers will include T-cell subsets, heat shock protein 90α, and cytokines (IL-6, IL-8, IL-17, CRP) to capture dynamic immune changes and identify potential predictive biomarkers for treatment response.

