### Statistical analysis

2.7

The sample size is calculated based on a Simon’s two-stage optimum design. The null hypothesis (P0) assumes a historical ORR of 5% for second-line treatment, while the alternative hypothesis (P1) anticipates an ORR of 20%. With a one-sided alpha of 0.05 and a beta of 0.2, the first-stage enrollment is 10 patients (n1 = 10), with a futility boundary of 0 responders (r1 = 0). The total planned enrollment is 29 patients (n = 29), with a rejection boundary of three responders (r = 3). Accounting for a 10% dropout rate, the total enrollment target is 32 patients.

Analyses will follow the intention-to-treat principle. The full analysis set and per-protocol set will be used for efficacy, while the safety analysis set will cover all patients who received at least one dose of the study drug.

Continuous variables will be presented as mean ± standard deviation or median with range, and categorical variables as frequencies and percentages. ORR and DCR will be reported with 95% Clopper-Pearson confidence intervals. Time-to-event endpoints (OS, PFS, DoR, TTP) will be estimated using the Kaplan-Meier method. Univariate and multivariable Cox proportional hazards models will be used to explore the impact of baseline characteristics and biomarkers on survival outcomes. Multivariable Cox regression models will include prior treatment characteristics as covariates to adjust for potential heterogeneity in baseline therapies. All statistical tests will be two-sided with a significance level of 0.05, performed using SPSS version 22.0 or higher.

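### The section 2.2 safety stop is not limited to treatment-related events, so as written one death from progression among the first 10 patients ends the study even if the go criterion is met

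*Protocol article*

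**What the plan says.** Section 2.2 (Study design) of the protocol article lists the decisions around the first 10 patients. The study stops if none of them responds. The next sentence adds: "The study will also be terminated in the event of unresolved SAEs or death". The one after that is the go rule: "If one or more patient achieves, the trial will proceed to phase II". The abstract repeats the go rule without any safety condition: "If at least one patient responds, the study will expand to a total of 32 patients".

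The safety stop gives no relation to treatment, no cause of death, no time by which an SAE must resolve, and no phase. No readable part of the article narrows it.

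Elsewhere the article does separate related from unrelated events. Section 2.1 lists SAEs and treatment-related adverse events as different categories, and section 2.6 ties JDB153 dose reduction to treatment-related events of grade 3 or higher. Section 2.1 also makes death an ordinary outcome of the trial: "OS is defined as the time from study enrollment to death from any cause".

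**The concern.** In advanced pancreatic cancer after failed systemic therapy, some deaths from progression are to be expected early on. A stop triggered by death of any cause therefore reacts to the disease as well as to the drugs.

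If the sentence is followed literally, a regimen with a response among the first 10 can be abandoned because one non-responder progressed and died. The stage-1 decision is then no longer the one for which 10 and 29 patients were chosen. If the sentence is instead set aside when such a death occurs, the choice to stop or continue an open-label, single-center trial is made case by case, after the outcome is known, against its own published rule.

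**Working it through.** **Inputs from the protocol article.** Section 2.7: P0 = 5%, P1 = 20%, "With a one-sided alpha of 0.05 and a beta of 0.2", n1 = 10 with r1 = 0, n = 29 with r = 3. Section 2.5: "Tumor response will be evaluated every 8 weeks according to RECIST version 1.1". Section 2.3: patients must "have a life expectancy of at least 12 weeks". Introduction: median OS in second line seldom above 7 months.

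**Step 1: the plan's own design.** The trial continues with X1 ≥ 1 response in 10 and rejects with at least 4 in 29, so P(reject) = Σ over x ≥ 1 of P(X1 = x) × P(X2 ≥ 4 − x), with X1 ~ Bin(10, p) and X2 ~ Bin(19, p).

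- At p = 0.20: x = 1 gives 0.2684 × 0.7631 = 0.2048; x = 2 gives 0.3020 × 0.9171 = 0.2770; x = 3 gives 0.2013 × 0.9856 = 0.1984; x ≥ 4 gives 0.1209. The sum is 0.801.
- At p = 0.05 the same sum is 0.047.
- Go probability at 20%: 1 − 0.8^10 = 0.893.

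The stated design reproduces.

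**Step 2: add the stop as written, on the narrow phase Ib-only reading.** Let q be the assumed risk that a patient dies of any cause before the stage-1 decision, independent of response. The trial survives the stop with probability (1 − q)^10, which multiplies both the go probability and the power.

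| Assumed q | P(at least 1 death in 10) = 1 − (1 − q)^10 | Go probability at ORR 20% | Power |
|---|---|---|---|
| 0 | 0 | 0.893 | 0.801 |
| 2% | 0.183 | 0.893 × 0.817 = 0.729 | 0.801 × 0.817 = 0.655 |
| 5% | 0.401 | 0.893 × 0.599 = 0.534 | 0.801 × 0.599 = 0.480 |

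If deaths fall only on non-responders, power is 0.660 and 0.490, so the independence assumption matters little.

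**Step 3: how wide the range is.** The article gives no accrual rate and no early hazard, so both are assumed. Median OS is set at 7 months, and patients enter at equal intervals. Four survival curves are used: S(t) = exp(−ln2 × (t/7)^k) with k = 1, 1.5 and 2, and a curve with no deaths before 12 weeks (2.76 months) followed by an exponential scaled to the same median. P(at least 1 death) = 1 − Π S(cut-off − entry time). The table gives the lowest and highest value over the four curves.

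| Assumed accrual per month | Deaths up to the tenth patient's 8-week scan | Deaths up to the tenth patient's entry |
|---|---|---|
| 1 | 99.8–99.9% | 98–99% |
| 2 | 91–98% | 48–89% |
| 3 | 71–96% | 4–77% |
| 5 | 32–93% | 0–59% |
| 10 | 0–90% | 0–36% |

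The second cut-off applies if the response that meets the go rule has already been seen when the tenth patient enters. From 2 per month upward the low ends come from the curve with no deaths before 12 weeks. The 2% and 5% risks in step 2 lie inside this range. They are not a lower limit: at 5 per month with no early deaths the first cut-off gives 32% and power 0.54, and at 10 per month it gives 0 and power 0.80.

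**The case against.** The strongest reply is that the sentence is an added safety stop, and a safety stop is meant to override an efficacy go. Section 2.2 has another of the same kind: "If DLT occur in one or more patients at the 500 mg BID dose level, the study will be terminated". That stands. A reader might infer that the stop and the go rule contradict each other, but the document does not support this: precedence of safety over efficacy is normal, and an abstract need not repeat every stop. The defect is the missing qualifier, which lets a disease event trigger a safety stop.

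A second reply is that treatment-related events are obviously meant. The sentence sits in the phase Ib text, overall survival counts all deaths, and survival follow-up is scheduled. The phrase can also be read as SAEs that are unresolved or fatal, with the SAE definition left to the full protocol, and the study-flow figure is not shown. This makes the benign reading likely. It does not remove the point, because the article prints the rule in mandatory and unqualified terms, while it does qualify events by relation to treatment in section 2.6.

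A third reply is that without an accrual rate the size of the effect is unknown. That also stands, and it is why step 2 is offered only as an illustration.

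**Conclusion.** The point holds as a badly worded stopping rule that should be fixed. Confidence is high about the wording and its literal consequence: one progression death among the first 10 ends the study whatever the number of responses, so the power of 0.801 and go probability of 0.893 no longer apply. The size of the loss is uncertain. At an assumed 5% or 2% death risk, power is about 48% or 65% and the go probability about 53% or 73%. Depending on accrual and early hazard, the chance that the rule fires runs from near 0 (very fast accrual, no deaths before 12 weeks) to over 99% (1 patient per month at a 7-month median).

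A reader might infer that the trial is almost certain to be stopped. The documents do not support that, since it needs slow accrual and a literal reading that is probably not the intended one. Nor is overall survival lost, because patients already enrolled could still be followed. If the rule was meant for the whole study rather than phase Ib, the exposure would be larger than shown here.

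**What to change.** Reword the stop in section 2.2 by amendment:

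- Restrict the trigger to treatment-related deaths and to treatment-related SAEs not resolved by a stated time.
- State whether it applies to phase Ib only or to the whole study.
- Say that deaths from disease progression are endpoint events and do not stop the trial.
- Make the go rule conditional on this safety stop not having been met, so that the order of the two rules is explicit.

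This needs no extra patients, visits or procedures, and the Simon boundaries (0/10, 3/29) are unchanged. The downside is that the stop then depends on attributing each death or SAE to treatment, which is a judgement. The protocol already relies on such attribution for JDB153 dose reduction in section 2.6.

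### If the starting dose is lowered after stage 1, the 4-of-29 rule still pools both doses, so the stated alpha and power do not hold for the dose carried forward.

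*Protocol article*

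**What the plan says.** All of this is in the protocol article.

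- **Study design (2.2), stage 1.** Ten patients start JDB153 at 600 mg BID. No response stops the study; one or more opens phase II.
- **Study design (2.2), dose change.** With more than one DLT in phase Ib, "the dose of JDB153 for the phase II cohort will be reduced to 500 mg orally BID". One or more DLTs at 500 mg BID ends the study.
- **Study design (2.2), counting.** "This phase will enroll additional patients to reach a total sample size of 32". The 10 stage-1 patients are therefore part of the total, whichever dose phase II uses.
- **Study design (2.2), final rule.** "If four or more responses are observed among the 29 evaluable patients", the null is rejected and the regimen is said to merit further study. No dose condition is attached.
- **Statistical analysis (2.7).** "The null hypothesis (P0) assumes a historical ORR of 5% for second-line treatment", the alternative is an ORR of 20%, and the design is set up thus: "With a one-sided alpha of 0.05 and a beta of 0.2". There is one pair of hypotheses and one set of boundaries (0 of 10, then 3 of 29).

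Neither section sets stage 1 aside after a dose change, requires any response at the lower dose, or says which dose the conclusion concerns.

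**The concern.** The error rates of a Simon two-stage design are computed for a single response probability common to both stages. This protocol plans a branch in which the two stages use different starting doses, then applies the single-probability rule to the sum. In that branch, responses at the first dose count towards a conclusion about a regimen whose next users would start lower. Low activity at the first dose likewise counts against the lower one, and the stage-1 futility look is made entirely on the first dose.

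At stake is what a positive or negative result would mean for the dose carried forward. The formal claim would carry an alpha and a power that were not calculated for it. An unseen analysis plan cannot be presumed to settle this, because the article itself states both the dose switch and the unconditional rule, in the same section.

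**Working it through.** **Inputs from the protocol article.** P0 = 0.05, P1 = 0.20, one-sided alpha 0.05, beta 0.2, n1 = 10, r1 = 0, n = 29, r = 3, enrolment 32 (all 2.7). The reduction is triggered by 2 or more DLTs in 10, and one DLT at the lower dose stops the study (both 2.2). Stage 2 therefore has 29 − 10 = 19 evaluable patients, or 32 − 10 = 22 enrolled.

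**Assumptions.** ORR by dose and DLT rates are not given, so ranges are shown. Response and DLT are treated as independent.

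**Formula.** With pA the ORR at the first dose and pB the ORR in stage 2,

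P(reject) = Σ over x = 1..10 of P(X1 = x; 10, pA) × P(X2 ≥ 4 − x; 19, pB),

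where the second factor is 1 for x ≥ 4.

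**Step 1: the plan's own figures.** With pA = pB = 0.05 the result is 0.0468; with pA = pB = 0.20 it is 0.8011. A search over two-stage designs returns 0/10 and 3/29 as the optimal one. The stated design is correct for one common response rate.

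**Step 2: lower dose at the null (pB = 0.05).** The chance that stage 2 supplies the missing responses is:

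| Stage-1 responses | Needed of 19 | Probability at 5% |
|---|---|---|
| 1 | 3 | 0.0665 |
| 2 | 2 | 0.2453 |
| 3 | 1 | 0.6226 |
| 4 or more | 0 | 1 |

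For pA = 0.20 the stage-1 probabilities of 1, 2, 3 and 4 or more responses are 0.2684, 0.3020, 0.2013 and 0.1209. So

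0.2684 × 0.0665 + 0.3020 × 0.2453 + 0.2013 × 0.6226 + 0.1209 = 0.0179 + 0.0741 + 0.1253 + 0.1209 = 0.338.

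The same sum for other values of pA:

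| ORR, first dose | ORR, lower dose | P(reject) |
|---|---|---|
| 5% | 5% | 0.047 |
| 10% | 5% | 0.122 |
| 15% | 5% | 0.222 |
| 20% | 5% | 0.338 |

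**Step 3: the other direction.** With pA = 0.05 and pB = 0.20, P(reject) = 0.320 against the planned 0.80. The main reason is that stage 1 stops for futility with probability 0.95^10 = 0.599.

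**Step 4: how often the branch is reached.**

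- Reduction triggered: 1 − (1 − d)^10 − 10d(1 − d)^9 = 0.26, 0.46 or 0.62 at DLT rates d of 10%, 15% or 20%.
- No DLT in 22 patients at the lower dose: (1 − q)^22 = 0.64, 0.32 or 0.10 at rates q of 2%, 5% or 10%.

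The requirement of at least one stage-1 response is already inside the formula. As an example, with d = 15%, q = 5% and ORRs of 20% and 5%, the unconditional chance of the feared outcome is 0.456 × 0.324 × 0.338 = 0.05.

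**Step 5: the reduced-dose cohort on its own** (single-stage binomial, once stage 2 has opened, 5% against 20%).

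| Rule | Alpha | Power |
|---|---|---|
| 3 or more of 19 | 0.067 | 0.763 |
| 4 or more of 19 | 0.013 | 0.545 |
| 4 or more of 22 | 0.022 | 0.668 |

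The last row applies only if all 22 enrolled patients are evaluable.

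**The case against.** Four points can be made for the plan as it stands.

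1. **The stated null concerns the regimen, not a dose.** If both doses have an ORR of 5%, alpha is 0.047 as designed, and equal response rates make pooling harmless. With 20% at the first dose the combination is active somewhere, so rejecting is not a false positive for the null as written. This stands, and it is why the point is limited to the dose carried forward. It does not remove the point, because the text never says which dose the conclusion covers.
2. **The 0.34 is an extreme case.** It assumes that a step from 600 to 500 mg takes the ORR from 20% back to 5%. No passage supports that; at 10% against 5% the figure is 0.12. This stands.
3. **The branch may rarely reach its final analysis**, because a single DLT at the lower dose ends the study. This stands too, and 0.34 should not be read without it.
4. **Exposure in stage 1 is not purely 600 mg**, since section 2.6 allows individual reductions. True, but the point concerns starting doses.

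A reader might infer that the lower dose could be declared promising on responses seen only at the first dose. The rule does permit this, since four responses in stage 1 already meet the final boundary. It needs 4 or more of 10, however, with probability 0.12 at an ORR of 20%, 0.013 at 10% and 0.001 at 5%. Partial carry-over from one to three stage-1 responses is the more usual route. A reader might also infer that the trial's overall type I error is 0.34. The documents do not support that either: the figure is conditional on the branch and on assumed response rates.

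**Conclusion.** The point holds in a conditional form. The design is correctly calculated for one common response rate. It is then applied unchanged in a branch, written into the same section, where the two stages start at different doses. In that branch alpha 0.05 and power 0.80 do not describe a test of the dose carried forward. Under the assumed ORRs, rejection with a lower-dose ORR of 5% ranges from 0.047 (no difference between doses) to 0.34 (first dose at P1), and success with an active lower dose can fall to 0.32.

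The practical reach depends on unknown DLT rates and may be small. This should be settled before stage-1 results are known; it does not invalidate the design when the starting dose is unchanged. No view is taken on which dose is right.

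**What to change.** In 2.2 and 2.7:

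- State that the 4-of-29 rule, with its alpha and power, applies only when all counted patients share one starting dose.
- If the starting dose changes after stage 1, report ORR with exact confidence intervals by starting dose, and make no formal claim about the reduced dose from the pooled count.
- Judge the reduced-dose cohort on its own evaluable count and restate its operating characteristics. For example, 4 or more of 19 evaluable gives alpha 0.013 and power 0.545; if all 22 are evaluable, 4 or more of 22 gives alpha 0.022 and power 0.67. Name the denominator, because the two differ materially.

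The cost is a short paragraph in each section and no extra patients. The real price is a stated power well below 0.80 in that branch, which the sponsor should acknowledge: 19 evaluable patients cannot give alpha of at most 0.05 with 80% power, and a single-stage test at one dose would need at least 27 (4 or more of 27: alpha 0.044, power 0.818).
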